#### **Discharge from the Transplantation Center**

- Register the number of re-operations using the data available in the CRF. Procedure codes from the surgical report should be used.
- For VAC treatment, register the duration of time with VAC.
- Register the echocardiography closest to the time of discharge.
- Days at the transplantation center are counted as the number of days from transplantation to discharge.

#### **SAE Monitoring**

- Serious Adverse Events (SAEs) are monitored during the first 28 days post-transplantation. SAEs can be repeated if multiple events occur in the same patient.

#### **Mortality Follow-Up**

- Mortality follow-up is conducted at 3 and 6 months post-transplantation.

#### **At 1 Year**

- Register the data available closest to 1 year post-transplantation.
- Primarily register data from examinations performed at the respective transplantation center.

## Study visit schedule

|                             | Inclusion | Transplantation | 24 h after tx                     | 7-14 days after tx | ICU discharge | Discharge from tx-ward | 3, 6 months after tx | 1 year after tx |
|-----------------------------|-----------|-----------------|-----------------------------------|--------------------|---------------|------------------------|----------------------|-----------------|
| Informed consent            | x         |                 |                                   |                    |               |                        |                      |                 |
| Background                  | x         |                 |                                   |                    |               |                        |                      |                 |
| Medical history             | x         |                 |                                   |                    |               |                        |                      |                 |
| Cardiac status at inclusion | x         |                 |                                   |                    |               |                        |                      |                 |
| Echocardiography            | x*        | x*              | x                                 | x*                 | x*            | x*                     |                      | x*              |
| Renal function              | x*        | x*              |                                   |                    |               |                        |                      | x*              |
| Cardiac catheterization     | x*        | x*              |                                   |                    |               |                        |                      | x*              |
| Cardiac status at tx        |           | x               |                                   |                    |               |                        |                      |                 |
| Perioperative data          |           | x               |                                   |                    |               |                        |                      |                 |
| Basic donor data            |           | x               |                                   |                    |               |                        |                      |                 |
| Hemodynamic data            |           |                 | x                                 |                    |               |                        |                      |                 |
| Days with MCS               |           |                 |                                   |                    | x             |                        |                      |                 |
| ICU interventions           |           |                 |                                   |                    | x             |                        |                      |                 |
| Repeated surgery            |           |                 |                                   |                    |               | x                      |                      |                 |
| Rejection                   |           |                 |                                   |                    |               | x                      |                      | x               |
| Events and time on ward     |           |                 |                                   |                    |               | x                      |                      |                 |
| Mortality check             |           |                 |                                   |                    |               |                        | x                    |                 |
| Coronary angiography        |           |                 |                                   |                    |               |                        |                      | x               |
| SAE                         |           |                 | Registered first 28 days after tx |                    |               |                        |                      |                 |

Tx; transplantation, inkl; inclusion, PGD; primary graft dysfunction, MCS; mechanical circulatory support, ICU; intensive care unit, SAE; serious adverse events

\* if data is available

### 4.3. Biological sampling procedures

No additional samples will be taken from the research subjects (e.g. the heart recipients).

In cases where it is logistically possible and permission has been granted, in accordance with current regulations, blood and heart tissue will be obtained from the organ donors for histological and biochemical analyses.

#### 4.3.1. Handling, storage, and destruction of biological samples

The hearts of organ donors that are not transplanted may be used for tissue analysis, when logistically feasible and permission is granted, in accordance with national regulations. The hearts will be examined for coronary heart disease and myocardial infarction. Tissue samples will be taken from several areas with affected (in such donors) and normal function. Histological analyses, Western blot, and analyses for proteomics are planned. The analyses are planned to be performed at Wallenberg lab as well as the Core facilities at Sahlgrenska Academy.

Blood samples from donors will be taken when logistically feasible and permission is granted, in accordance with current regulations. Blood samples are planned to be analyzed by enzyme-linked immunosorbent assay (ELISA). The analyses are planned to be performed at Wallenberg lab and Lab of immunology, Sahlgrenska Academy.

Samples will be saved up to 10 years after the study has ended.

#### 4.3.2. Total volume of blood per study subject

No blood will be taken from the recipients.

From the donors, 20 ml blood is planned to be taken on up to three occasions, i.e. a total of 60 ml blood. Blood samples for analysis of troponin T and NTproBNP will be taken as part of normal healthcare routines and destroyed immediately after analysis.

#### 4.3.3. Biobank

All samples taken in this study are registered in a biobank at Biobank West and handled according to current biobank laws and regulations. The law regulates the way in which samples can be stored and used as well as rules on quality and security for biobanks. The samples are coded/pseudonymized to protect the research subjects' identification. All samples and the identification list/code list are stored securely and separately to prevent unauthorized person from having access to them.

#### 4.4. End of study

The study ends when the following two criteria are met. (1) 445 patients heart-transplanted patients are included of which (2) at least 89 patients have received a heart with impaired function. The study will continue until both criteria are met.

The study may be prematurely terminated if it appears that the treatment involves a large number of undesirable severe adverse events or if recruitment of research subjects cannot be met within reasonable time limits.

Decisions on premature termination are taken by the sponsor.

### 5. Subject selection

#### 5.1. Inclusion criteria

To be included in the study, research subjects must meet the following criteria:

- Patient who has been accepted for heart transplantation at the participating transplantation center
- The research subject has given written consent to participate in the study
- Aged 18 years or older

We refer to research subjects only as those who are heart recipients in this study; the heart donors are not considered research subjects since they are deceased.

#### 5.2. Exclusion criteria

The study has the following exclusion criteria:

- Mental inability, reluctance or language difficulties that result in difficulty understanding the meaning of study participation
- Another study, where the patient is included, which is not considered compatible with the current study.

### 6. Handling of adverse events

#### 6.1. Definitions

##### 6.1.1. Adverse Event, AE

After heart transplantation, a patient usually requires intensive care with circulatory support, respiratory care, and often dialysis. Such treatment is part of the usual course following heart transplantation and will therefore be difficult to assess as unwanted adverse events. We have therefore not defined any adverse events.

### 6.1.2. Serious Adverse Event, SAE

Serious unwanted events include conditions that require more invasive measures or death. SAE include:

- Need of postoperative mechanical assistance more than 24 hours post-op
- Death within 28 days from transplantation
- Other event that resulted in prolonged care time or suffering for the patient (e.g., stroke with sequelae) that can be attributed to, or is suspected to be attributable to, cardiac function of the donor

## 6.2. Assessment of adverse events

### 6.2.1. Assessment of causal relationship

We believe that AE and SAE will be difficult to attribute to cardiac function of the organ donor. Each SAE in particular will be analyzed in the case there may be a causal relationship with the cardiac function of the organ donor. The incidence of AE and SAE between groups will be analyzed in interim analyses.

## 6.3. Reporting and registration of adverse events

### 6.3.1. Reporting of adverse events (AE)

AE will not be reported (see above).

### 6.3.2. Reporting of serious adverse events (SAE)

Serious adverse events (SAE) will be reported to the sponsor on a special SAE form within 24 hours of the investigator being informed of the SAE.

Follow-up information describing the outcome and handling of the SAE is reported as soon as this information is available. The original should be kept in the Investigator Site File.

## 6.4. Follow-up of adverse events

In case of increased frequency of SAE at the interim analysis, the study may be discontinued.

## 6.5. Independent Data Monitoring Committee

Since the study is not blinded or randomized, no independent safety committee is planned.

# 7. Statistics

## 7.1. Analysis population

The primary variable will be calculated for those patients who are transplanted (per protocol). For some secondary variables (time to transplantation, estimation of the number of increased transplantations), people who were not transplanted will also be included in the analysis (intention to treat).

## 7.2. Statistical analyses

### 7.2.1. Statistical methods

The primary variables will be analyzed with binary logistic regression. The primary outcome variable will be incidence of death, re-transplantation or need of long-term mechanical assistance within one year after transplantation. The primary explanatory variable is incidence of cardiac dysfunction in the donor, defined as regional hypokinesia and/or ejection fraction < 50%. The analysis will be adjusted for age of recipient, age of donor, need of mechanical assistance before transplantation and "urgent call" status of transplantation.

For statistical significance, the p-value must be  $> 0.05$ .

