## 7.4. Sample size calculations

This is a non-inferiority trial. Power calculations are made based on non-inferiority calculations. Based on our retrospective data, the absence of death/retransplantation within a year was 90%. We have calculated power to exclude a difference in the primary outcome of 10%, which is the benefit that may be relevant since patients can be transplanted earlier and more patients can be transplanted. We expect that 20% of the transplantations will come from hearts with dysfunction. The power calculation says then that we need 445 transplanted hearts and at least 89 transplanted hearts with dysfunction. Since we do not know the exact incidence, outcome, or transplantation frequency of hearts with dysfunction in a prospective cohort, we primarily plan to include 500 heart-transplanted patients in the study.

To be able to answer our specific research questions about the heart donors, we estimate that we need at least 100 donors of hearts with dysfunction to be able to have a representative group. With an estimated incidence of cardiac dysfunction in 25% of the donors, at least 400 possible heart donors are needed in the study. However, the study intends to continue collecting data from all donors until the primary objective is answered.

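### The trial is sized to exclude an absolute 10-point difference, but the primary logistic analysis as written contains no rule that tests that margin

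*Protocol*

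**What the plan says.** Section 7.4 sets the hypothesis: "This is a non-inferiority trial. Power calculations are made based on non-inferiority calculations". It then gives the planning inputs: "Based on our retrospective data, the absence of death/retransplantation within a year was 90" per cent, "We have calculated power to exclude a difference in the primary outcome of 10" per cent, and "We expect that 20% of the transplantations will come from hearts with dysfunction". The result is that "we need 445 transplanted hearts and at least 89 transplanted hearts with dysfunction". Because incidence and outcome are uncertain, it adds that "we primarily plan to include 500 heart-transplanted patients in the study".

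Section 7.2.1 fixes the analysis: "The primary variables will be analyzed with binary logistic regression". The explanatory variable is donor cardiac dysfunction. "The analysis will be adjusted for age of recipient, age of donor, need of mechanical assistance before transplantation", and for urgency status. The section then gives a p-value threshold for significance and nothing more. It names no effect measure, repeats no margin and sets no confidence bound.

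Section 7.5, on interim looks, is the only other place that says how a group difference in the primary outcome is judged. It uses 10 percentage points in absolute terms, together with a p-value.

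**The concern.** A non-inferiority conclusion needs three things on one scale: an estimate, a confidence limit and a margin. Section 7.4 supplies the margin as a difference in percentages. The coefficient that Section 7.2.1 produces for donor dysfunction is a log odds ratio, and by default its p-value tests an odds ratio of 1. Whichever way the inequality in the p-value rule is read, it does not refer to 10 points. Followed literally, the plan would end without a statement on whether a 10-point excess has been excluded, which is the question the trial was sized to answer.

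The missing link also leaves a choice open. An analyst could compare an odds ratio with a converted margin, or derive a risk difference from the same model. The two routes differ in power and in how much excess risk they tolerate, and the study is unblinded with repeated interim analyses.

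**Working it through.** **Inputs from the protocol.** Event rate 10% (90% event-free, Section 7.4); margin 10 points; 20% dysfunction hearts, so 1:4; 445 in total with 89 dysfunction hearts, hence 356 with normal function; 500 planned, hence about 400 versus 100. Equal true rates are assumed, as the background section expects no effect on outcome. The protocol states neither alpha nor power for the sample size.

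**Reproducing 445/89.** Unpooled risk-difference formula, one-sided 0.025, 80% power:

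- n(normal) = (0.09 + 0.09/0.25) × (1.960 + 0.842)² / 0.10² = 353.2
- n(dysfunction) = 353.2/4 = 88.3, rounded up to 89; 5 × 89 = 445, exact.
- Other settings do not fit: 0.025 with 90% power gives 595, 0.05 with 80% gives 350, and 0.05 with 90% gives 485.

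So the margin is an absolute risk difference, and 80% power at one-sided 0.025 is inferred from the match.

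**Power on the risk-difference scale.** SE = √[0.09 × (1/356 + 1/89)] = 0.0356. Power = Φ(0.10/0.0356 − 1.96) = Φ(0.853) = 80.3%.

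**Power if the margin is converted to an odds ratio.** At 10% versus 20%, OR = (0.20/0.80)/(0.10/0.90) = 2.25 and ln 2.25 = 0.811. SE = √[1/(356 × 0.09) + 1/(89 × 0.09)] = 0.395. Power = Φ(0.811/0.395 − 1.96) = Φ(0.093) = 53.7%. For 80% power, 166 dysfunction hearts (830 in total) would be needed.

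| Equal true rates of 10% | 356 vs 89 | 400 vs 100 |
|---|---|---|
| Risk difference, formula | 80.3% | 84.6% |
| Risk difference, unadjusted Wald, simulated | 77.1% | 81.7% |
| Risk difference standardised from the adjusted model, two simulations | 76.8% and 78.7% | not run |
| OR < 2.25, Wald formula | 53.7% | 58.6% |
| OR < 2.25, unadjusted Wald, simulated | 55.0% | 60.8% |
| OR < 2.25, likelihood-ratio test, exact enumeration | 59.8% | 64.6% |
| OR < 2.25, adjusted Wald, two simulations | 50.4% and 54.6% | not run |

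The adjusted rows rest on assumed covariate effects, since the protocol gives none. If the margin is re-converted at each reference rate, odds-ratio power at 445 runs from 56% (8% events) to 48% (15% events). Risk-difference power runs from 87% to 66%.

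**What a fixed OR of 2.25 would mean.** Excess risk = 2.25·o/(1 + 2.25·o) − p, with o = p/(1 − p):

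- p = 8%: 16.4% − 8% = 8.4 points
- p = 15%: 28.4% − 15% = 13.4 points
- p = 20%: 36.0% − 20% = 16.0 points

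A control rate above 10% is plausible: the 90% figure covers death and retransplantation only, while the primary outcome in Section 3.3 also counts mechanical assist.

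**Error rate at the margin.** With true rates of 10% and 20%, simulated false non-inferiority at 356 versus 89 (nominal 2.5%) was 3.9% for the unadjusted Wald risk difference and 2.1% for the Wald odds ratio. For the likelihood-ratio odds-ratio test it was 2.6% by enumeration. Part of the gap between 80% and 54% therefore reflects Wald behaviour rather than scale. A score-type risk-difference test uses the variance at the margin. The constrained rates are about 8.8% and 18.8%, so SE₀ = √(0.088 × 0.912/356 + 0.188 × 0.812/89) = 0.0441. Power = Φ((0.10 − 1.96 × 0.0441)/0.0356) = Φ(0.38), about 65%.

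**The case against.** The strongest reply is that the protocol fixes a model, not an effect measure. It never mentions an odds ratio, and the absolute wording in Section 7.5 points to the risk-difference scale. A logistic model can deliver a risk difference, and the details of doing so are often left to a statistical analysis plan, which may exist but is not at hand.

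Much of this stands. A reader might infer that logistic regression cannot test a 10-point margin. That is not so: standardising predictions from the same adjusted model gives a marginal risk difference with an interval, and the margin can be tested directly at close to the planned power. A reader might also infer that the trial has 54% power rather than 80%. The documents do not support that either. Neither 2.25 nor 80% appears in the protocol, and 54% belongs to one assumed decision rule at the minimum sample size, not to the plan as written.

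What does not stand is the claim that only a technical detail is missing. The protocol itself states the hypothesis, the margin, the model and a decision rule, and that rule does not use the margin. Interval methods and software can wait for an analysis plan. The criterion for the trial's main conclusion has already been written down, and it does not answer the non-inferiority question.

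**Conclusion.** The point holds as a mismatch between two stated elements: Section 7.4 sizes the trial on an absolute 10-point risk difference, and the analysis and decision rule in Section 7.2.1 do not test it. This rests on the text and on the exact reproduction of 445/89, not on any power figure.

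The power loss is conditional. It assumes a 10% reference event rate, equal true rates, conversion of the margin to an odds ratio of 2.25, and a one-sided 0.025 test. The size of the gap also depends on the interval method, as the error rates at the margin show. The 8.4 to 16.0 point drift likewise applies only if a fixed odds-ratio margin were adopted. The mismatch concerns the primary conclusion and should be resolved before the primary analysis. The p-value threshold in Section 7.2.1 needs correcting in its own right, but that is a separate error.

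**What to change.** In Section 7.2.1, keep the logistic model and its covariates and replace the p-value rule. Define the primary estimate as the standardised (marginal) risk difference from that model, dysfunction minus normal, with a delta-method or bootstrap interval. Conclude non-inferiority only if the upper limit of the two-sided 95% confidence interval is below 10 percentage points. Report the odds ratio as secondary. In Section 7.4, say that the margin is absolute and state the alpha and power used.

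Name the interval method in advance, check its error rate at the margin by simulation, and add an unadjusted score-type interval (Farrington-Manning or Miettinen-Nurminen) as a sensitivity analysis, knowing that it is the stricter test.

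The cost is a few sentences and a little more analysis work, with no extra data or patients. Simulated power at 445/89 is about 77–79%, slightly below the formula's 80%, so the sample size roughly stands; the planned 500 gives some reserve. If strict control at 2.5% through a score-type interval were made primary, power at 445/89 would be nearer 65% and the size would need another look. The alternative, a pre-set odds-ratio margin of 2.25, would need about 830 patients for 80% power.

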|-----------------|---------------------------------------------------------------------------------------------------------------------------------------------------------------------------------------------------------------------------------------------------------------------------------------------------------|
|                 | Another study, where the patient is included, which is not considered compatible with the current study.                                                                                                                                                                                                |
| Study outcomes: | 
Primary variable: Death, retransplantation or need of mechanical assist one year after the heart transplantation.
 
Secondary variable: Left-ventricular moderate or severe primary graft dysfunction
 
The study has several secondary objectives that are presented in the protocol.
 |
| Study period:   | Q2 2020 – Q2 2027                                                                                                                                                                                                                                                                                       |

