### 3.3. Primary variable

The primary variable is: Death, retransplantation or need of a mechanical assist one year after heart transplantation.

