### 3.4. Secondary variable

The secondary variable is: frequency of left-sided moderate or severe primary graft dysfunction (PGD).

Moderate PGD is defined as having *at least one of the following at 24 hours after cross-clamp release*:

- Ejection fraction  $\leq 40\%$ , *or* hemodynamic compromise with right atrial pressure (RAP)  $> 15\text{mmHg}$ , pulmonary capillary wedge pressure  $> 20\text{mmHg}$ , cardiac index  $< 2.0$ , hypotension with a mean arterial pressure  $< 70\text{mmHg}$   
*And at least one of the following:*
- High-dose inotropes (Inotrope score  $> 10$ ) *or* newly placed intra-aortic balloon pump.

Severe PGD is defined as dependence on left or biventricular mechanical support in the form of either ECMO, LVAD, BiVAD, or percutaneous LVAD at 24 hours after cross-clamp release.

The following outcome variables apply to the secondary research questions:

Need for interventions and complications in the postoperative course including, for example, mechanical heart pump, intra-aortic balloon pump, need for mechanical ventilation, need for dialysis, dose and time with inotropic and vasoactive medications.

Occurrence of ICD codes for cardiovascular disease in the Patient and Cause of Death registries for participating patients at 3, 5, and 10 years after transplantation.

Levels of cardiac biomarkers, occurrence of specific echocardiographic changes, ECG changes, and clinical data in donors with recovered and non-recovered cardiac function during the donation process, respectively.

Levels of cardiac biomarkers, occurrence of specific echocardiographic changes, ECG changes, and clinical data in donors with primary and non-primary heart disease, respectively.

Estimation of the number of extra patients who would be able to receive a heart transplantation with a systematic utilization of donor hearts with dysfunction.

Presence of specific histological changes and specific proteins in heart tissue with dysfunction and normal function, respectively.

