#### *Follow-up of recipients*

Recipient baseline data, including demographics and medical history, is recorded at inclusion. The recipients will be followed regarding death, need of mechanical heart pump and re-transplantation during the first year (primary outcome variable). Short-term data will be collected regarding need of post-operative mechanical assistance, intra-aortic balloon pump, dialysis, time with mechanical ventilation, inotropic drugs, re-surgery(s), time at the ICU, time at the home clinic/other department, time before returning home. The recipients will be followed according to clinical routine at the participating center, and no extra examinations are planned, with the exception that echocardiography is preferable performed at  $24 \pm 6$  hours for assessment of PGD.

The active follow-up end at one year after transplantation. Long-term complications that will be followed are death, need for mechanical heart pump, re-transplantation, rejection/coronary vasculitis, other organ failure. To investigate whether recipients of hearts with dysfunction have increased risk for other disease, data will be collected from the Swedish National Board of Health and Welfare's (Socialstyrelsen) Patient Register and Cause of Death Register. Those data that will be requested are all of the patients' ICD codes and medical procedure codes at 1, 3, 5, and 10 years after transplantation. Data may be collected from other national registers if they are available.

A list of variables is available in *Attachment 2*.

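### The mechanical-assist part of the primary endpoint is worded in three ways, and the 90% event-free rate behind 445/89 leaves that part out

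*Protocol*

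**What the plan says.** The protocol states the primary endpoint four times.

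- Synopsis: "Death, retransplantation or need of mechanical assist one year after the heart transplantation".
- Section 3.3: "Death, retransplantation or need of a mechanical assist one year after heart transplantation".
- Section 4.1, follow-up of recipients: "death, need of mechanical heart pump and re-transplantation during the first year (primary outcome variable".
- Section 7.2.1: "incidence of death, re-transplantation or need of long-term mechanical assistance within one year after transplantation".

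The first two put no limit on device or duration. The third names a heart pump. The fourth restricts the component to long-term assistance, and the protocol does not define long-term.

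Temporary support after surgery is expected. Section 3.4 says "Severe PGD is defined as dependence on left or biventricular mechanical support in the form of either ECMO", or an LVAD, BiVAD or percutaneous LVAD, at 24 hours. Section 6.1.2 lists post-operative mechanical assistance beyond 24 hours as a serious adverse event.

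For the sample size, section 7.4 says "Based on our retrospective data, the absence of death/retransplantation within a year was 90" per cent. Mechanical assist is not mentioned there. The margin is 10%, the expected share of hearts with dysfunction is 20%, and the result is 445 transplanted patients with at least 89 in the dysfunction group. The section plans to include 500 because incidence, outcome and transplantation frequency are uncertain. Section 4.4 still ends the study once 445 and 89 are reached.

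**The concern.** Two separate things are at stake.

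The first is which patients count. Early graft failure that needs support is a plausible harm of a donor heart with impaired function, so including or excluding temporary support bears directly on the comparison. The study is neither randomized nor blinded and has no independent safety committee (6.5). Interim analyses run after 100 patients and then after every 50 (7.5), with a stopping rule based on this outcome, and the sponsor decides on early termination (4.4). If the wording is not settled beforehand, the choice between sections could be made when results by group are already known.

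The second is whether the sample size belongs to the endpoint that will be analysed. The planning rate covers two components and the analysis covers three. In any given cohort, adding a component cannot lower the event rate. With a fixed absolute margin, a rate that rises from 10% towards 50% increases the variance and lowers power.

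**Working it through.** **Classification under each wording.** Take a recipient on ECMO at 24 hours who is weaned after some days and is alive with the same graft at one year.

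| Place | Primary event? |
|---|---|
| Synopsis, 3.3 | Yes, if the text covers the whole first year: no limit on type or duration |
| 4.1 | Unclear. It lists post-operative mechanical assistance separately as short-term data, which suggests no; but 3.4 uses the term mechanical heart pump for post-operative interventions, which suggests yes |
| 7.2.1 | No, on the ordinary meaning of long-term, which is undefined |
| 3.4 / 6.1.2 | Severe PGD, and an SAE if support lasted more than 24 hours |

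**How much one patient weighs.** At 10% events the dysfunction group has 89 × 0.10 = 8.9 expected events. One reclassified patient moves its rate by 1/89 = 1.1 percentage points. At the first interim, 20% of 100 gives about 20 such recipients, so one patient moves the rate by 1/20 = 5 points. The stopping rule asks for a 10-point excess together with p < 0.05.

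**Reproducing 445/89.** Inputs from 7.4: event rate 0.10 in both groups, margin 0.10 (read as absolute), allocation 1:4. Assumed, because 7.4 states neither: one-sided 2.5% and 80% power.

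n (dysfunction) = p(1−p)(1 + 1/4)(z₁ + z₂)² / margin² = 0.10 × 0.90 × 1.25 × (1.960 + 0.842)² / 0.10² = 88.3, rounded up to 89. Then 89 × 5 = 445.

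Other usual settings do not give this figure: one-sided 2.5% with 90% power gives 595, one-sided 5% with 80% gives 350, and one-sided 5% with 90% gives 485. The stated size is therefore correct arithmetic for a 10% event rate.

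**Effect of a higher composite rate.** The documents give no rate for mechanical assist, so the total rate p below is an assumption, taken as equal in both groups.

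Power = Φ(0.10 / √[p(1−p)(1/n₁ + 1/n₂)] − 1.960)

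For 89/356 and p = 0.12: √[0.1056 × (1/89 + 1/356)] = 0.0385; 0.10/0.0385 − 1.960 = 0.637; Φ = 0.738.

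| Composite rate | Power at 445 (89/356) | Power at 500 (100/400) | Size for 80% (total/dysfunction) |
|---|---|---|---|
| 8% | 87.5% | 90.9% | 365/73 |
| 10% | 80.3% | 84.6% | 445/89 |
| 11% | 76.9% | 81.6% | 485/97 |
| 12% | 73.8% | 78.6% | 520/104 |
| 15% | 65.7% | 70.7% | 630/126 |

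**Break-even at 500.** For 80% power, p(1−p) × (1/100 + 1/400) = (0.10/2.802)², so p(1−p) = 0.102 and p is about 11.5%.

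All of these are unadjusted comparisons of two proportions. The planned analysis is logistic regression with four covariates, so the figures are approximations.

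**The case against.** The strongest reply is that 7.2.1 governs the analysis and is clear on components and window, that 4.1 agrees with it on the window, and that temporary support is already captured as PGD, as an SAE and as short-term data. On this view the remaining differences are loose wording, and a device list or a definition of long-term may sit in a statistical analysis plan that is not shown. Part of this stands: the separation that 7.2.1 implies is largely in place. But the protocol itself states the primary variable in wordings that disagree, and section 10 treats a change of primary variable as a substantial amendment.

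Three stronger readings are tempting and are not supported.

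- A reader might infer that 445/89 fails its intended power. The protocol states no intended power, and the figure reproduces at 80%. The shortfall depends on an assist rate that the documents do not give. It may be small if only long-term devices count, or if most such patients also die or are retransplanted. The planned 500 absorbs a rate of up to about 11.5%.
- A reader might take the synopsis and 3.3 to mean status at one year, which would add a conflict over timing. Sections 4.1 and 7.2.1 both describe the first year as a whole, and for death the two readings coincide. It is more likely loose wording, to be aligned in the same edit.
- A reader might infer from the visit schedule that support and retransplantation are not collected at one year. Section 4.1 promises this follow-up, and the variable list in Attachment 2 is not shown.

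**Conclusion.** The concern holds on two counts. The mechanical-assist component is defined inconsistently between the synopsis and 3.3, 4.1, and 7.2.1, so temporary post-operative support may or may not be a primary event, and the stopping rule in 7.5 inherits the ambiguity. This needs correcting even if the effect on power proves small. Separately, the event-free rate in 7.4 omits one component of the endpoint to be analysed.

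The size of the second problem is conditional. If the composite rate stays at 10%, nothing is lost. Above 10%, power at 445/89 drops below the implied 80%. This rests on assumed alpha, power and composite rates, equal true rates in the two groups, and no covariate adjustment. Including 500 gives some protection, but section 4.4 does not require it.

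**What to change.** Adopt one definition that fixes the type of support, its duration and the window (within one year). Use it word for word in the synopsis, 3.3, 4.1 and 7.2.1, and refer to it in 7.5. One coherent choice is the 7.2.1 wording with long-term defined, and temporary support kept as a PGD and SAE outcome. The essential requirement is a single definition, settled without reference to results by group.

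Then take the one-year rate of that same composite from the existing retrospective data. In 7.4, state that rate, the one-sided alpha, and the resulting power at both 445 and 500.

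The cost is amendment text with ethics approval and one query of data already held. The stated power may become less favourable. No extra patients are requested, so if the composite rate does exceed 10%, the change discloses the loss of power and does not remove it.
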